**Statistical analysis**

To determine whether randomisation is successful, prognostic similarity (perinatal and nutritional characteristics) between treatment groups is assessed. The Students’ t-test, Mann-Whitney U test, and chi-square test or Fisher’s exact test are used to compare continuous normally distributed, nonparametric continuous and dichotomous data respectively.

Logistic regression is performed to examine whether acidic and neutral oligosaccharide supplemented enteral nutrition decreases the incidence of serious infections. In an additional analysis, adjustments are made for possible confounding factors as administration of antenatal corticosteroids, birth weight <p10, administration of breast milk and other prognostic factors that may be different between treatment groups.

Analyses of secondary outcomes (only crude) is performed by Mann-Whitney U test, chi-square test or Fisher’s exact test and log rank test for nonparametric continuous, dichotomous data and time-dependent data respectively.

Generalised estimated equations for longitudinal analysis24 are used to analyse changes over time in intestinal permeability, faecal microflora, faecal IL-8 and calprotectin, and plasma Th1/Th2 cytokine concentrations.

Distribution of optimal and non-optimal neuromotor development and normal and abnormal mental/motor development in oligosaccharides and control groups is examined by logistic regression with adjustments for possible confounding factors as gestational age and birth weight.

All statistical analyses are performed on an intention to treat basis. In addition, alternative per protocol analyses are performed, excluding all patients who are not treated according to protocol, defined as more than 3 consecutive days or a total of 5 days on minimal enteral feeding or without supplementation. For all statistic analyses a p value <0.05 is considered significant (two-tailed). SPSS 12.0 (SPSS Inc., Chicago, IL, USA) and STAT 7.0 (StatCorp LP, College Station, TX, USA) are used for data analysis.

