## Treatment allocation and blinding

To balance birth weight distribution into treatment groups, each infant is stratified to one of three birth weight groups (<799 g, 800-1199 g, ≥1200 g) and randomly allocated to treatment <48 hours after birth. An independent researcher uses a computer-generated randomisation table based on blocks of four (provided by Nutricia Nederland BV, Zoetermeer, The Netherlands) to assign infants to treatment A or B, which correspond to batch numbers on the nutrition products. Investigators, parents, medical and nursing staff are unaware of treatment allocation. The code for the batch numbers is broken after data analysis is performed.

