**Sample size**

Based on the differences (76% and 50% respectively) in infectious morbidity in the GEEF study,14 and a two-tailed α=0.05, β=0.20, a sample size of 2 x [2*7.85*0.63(0,37)]/(0,26)2 = 2 x 54 infants was calculated.

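### The primary logistic regression omits the birth-weight strata used at randomisation, so its test is somewhat conservative and gives up some power if birth weight predicts serious infection.

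*Protocol*

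**What the plan says.** **Randomisation** (Protocol, Treatment allocation and blinding). The stated purpose is to balance birth weight between the arms: "each infant is stratified to one of three birth weight groups (<799 g, 800-1199 g, ≥1200 g) and randomly allocated to treatment". The list is a "computer-generated randomisation table based on blocks of four".

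**Primary analysis** (Protocol, Statistical analysis). "Logistic regression is performed to examine whether acidic and neutral oligosaccharide supplemented enteral nutrition decreases the incidence of serious infections". This sentence names no covariate. The next one places adjustment in an additional analysis, so the primary model reads as treatment only. The adjusters named there are antenatal corticosteroids, birth weight <p10 and breast milk, plus other prognostic factors that may differ between the arms.

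**Secondary analyses** (same section). "Analyses of secondary outcomes (only crude) is performed by Mann-Whitney U test", with chi-square, Fisher and log-rank tests for the other data types. The neurodevelopmental outcomes are an exception: their logistic models adjust for gestational age and birth weight.

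**Sample size** (Protocol, Sample size). "Based on the differences (76% and 50% respectively) in infectious morbidity in the GEEF study", with "two-tailed α=0.05, β=0.20", leads to "2 x [2*7.85*0.63(0,37)]/(0,26)2 = 2 x 54 infants was calculated". The formula compares two proportions and has no stratification term.

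**The concern.** The trial balances its arms on birth weight and then analyses the primary outcome as if it had not. Birth weight <p10 does not fill the gap: it measures size for gestational age, and the strata are bands of absolute weight. The rule that brings in other factors when the arms may differ works against the strata too, because stratified blocks make a birth-weight difference unlikely. The protocol itself treats birth weight as important, since it stratifies on it and adjusts the neurodevelopmental models for it.

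At stake is efficiency. When a balanced factor is prognostic, a test that ignores it tends to reject a true null less often than its nominal level and detects a real effect less often than it could. The sample size leaves almost nothing above 80% power, so even a few points obtained from data already recorded are worth having.

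The stratum limits also have a hole: 799 g is neither below 799 g nor within 800-1199 g.

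**Working it through.** **1. The plan's own figure.** Inputs from the Sample size section: 76% and 50%, mean 63%, difference 0.26, two-tailed α = 0.05, β = 0.20, multiplier 7.85.

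- Protocol formula: 2 × 7.85 × 0.63 × 0.37 / 0.26² = 3.660 / 0.0676 = 54.1, so the stated 54 per arm reproduces.
- Pooled two-proportion formula: [1.960 × √(2 × 0.63 × 0.37) + 0.842 × √(0.76 × 0.24 + 0.50 × 0.50)]² / 0.26² = 52.9, so 53 per arm.
- Power with 54 per arm: Φ[(0.26 × √54 − 1.338) / 0.658] = Φ(0.870) = 80.8%.

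The unadjusted comparison therefore meets its target.

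**2. Effect of leaving the strata out.** From the protocol: 108 infants, three strata, blocks of four (taken as 1:1), marginal risks of 76% and 50%. Assumed, because the protocol gives neither: stratum shares of 20/40/40% (lightest to heaviest) and the stratum odds ratios of infection below. There were 20,000 simulated trials per setting, each with two-sided Wald tests from logistic models without and with stratum indicators.

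| Stratum odds ratios | Control risks, % | Type I error, crude / adjusted, % | Power, crude → adjusted, % | Gain, points |
|---|---|---|---|---|
| 1/1/1 | 76/76/76 | 4.8 / 4.9 | 80.4 → 81.2 | 0.8 |
| 2/1.4/1 | 83/77/71 | 4.7 / 4.9 | 80.5 → 81.9 | 1.3 |
| 4/2/1 | 89/80/66 | 4.4 / 5.0 | 81.1 → 83.3 | 2.3 |
| 9/3/1 | 93/82/61 | 3.8 / 4.9 | 81.8 → 85.5 | 3.8 |
| 25/5/1 (extreme) | 97/86/55 | 3.0 / 4.7 | 83.7 → 89.4 | 5.7 |

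Gains are taken from unrounded results. The first row shows 0.8 points even when the strata predict nothing, so most of the gain in the second row cannot be credited to prognosis.

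**3. Where the power goes.** Median log odds ratio and median model standard error (SE) under the planned effect, with the sampling SD of the crude estimate:

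| Stratum odds ratios | Crude estimate (SE) | Adjusted estimate (SE) | Sampling SD of crude estimate |
|---|---|---|---|
| 2/1.4/1 | −1.163 (0.421) | −1.207 (0.430) | 0.430 |
| 4/2/1 | −1.169 (0.421) | −1.259 (0.442) | 0.424 |
| 9/3/1 | −1.163 (0.420) | −1.351 (0.462) | 0.408 |
| 25/5/1 | −1.169 (0.420) | −1.523 (0.499) | 0.384 |

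Adjustment raised the SE in every simulated trial. It gains power because the estimate moves away from zero by more than the SE grows. At 9/3/1 the estimate grows by 1.351 / 1.163 = 1.16 and the SE by 0.462 / 0.420 = 1.10, so the ratio of estimate to SE rises from 2.77 to 2.92. At 4/2/1 it rises from 2.78 to 2.85.

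**4. Can the data carry the larger model?** At a mean risk of 63%, 108 infants give about 68 with infection and 40 without. That is adequate for one treatment term and two stratum terms.

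**The case against.** The best defence is that the plan is coherent as it stands. The sample size is for an unadjusted comparison, the primary test is unadjusted, power is 80.8%, and type I error stays at or below 5%. Nothing is invalid. All of this stands and limits the point to efficiency.

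The size also depends on inputs that the protocol does not supply. Weak to moderate strata give about 1 to 2 points, and larger gains need strongly prognostic strata. That stands too.

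A separate analysis plan may add the strata. The point therefore covers only what the protocol fixes: adjustment as an additional analysis, named adjusters without the strata, and mostly crude secondary tests.

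Three stronger readings are tempting but unsupported:

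- *The crude SE is too large because between-stratum variation enters the error term.* That is how a linear model behaves. In a logistic model, omitting a prognostic stratum makes the SE smaller (0.42 against 0.43-0.50) and pulls the odds ratio towards 1. The crude SE exceeds its own sampling SD only with strong strata (9/3/1 and beyond).
- *Every crude secondary test loses power in the same way.* The loss depends on how well birth weight predicts each outcome, and none of these outcomes was simulated.
- *Siblings require a primary model clustered on mother.* The protocol allocates each infant and nowhere says that siblings share an arm. Under individual allocation, with assumed rates of multiples and correlation, the naive SE is within about 1.5% of the correct one. Clustering is optional.

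**Conclusion.** The point holds as one of efficiency. The primary model omits the factor on which the trial randomises, and the additional model substitutes a different variable. If birth weight predicts serious infection, the crude test is somewhat conservative. With assumed shares of 20/40/40% and odds ratios from 2/1.4/1 to 9/3/1, type I error is about 4.7% to 3.8% and about 1 to 4 points of power are forgone; at 25/5/1 the figures are 3.0% and about 6 points. The direction was the same in every setting simulated, but the true size cannot be determined from the protocol. A reader should not infer that the trial is underpowered or its primary test invalid. The 799 g gap is a small textual error that needs no assumption.

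**What to change.** - **Primary analysis.** Logistic regression of serious infection on treatment and birth-weight stratum as randomised. State that the odds ratio is conditional on stratum, since it will lie further from 1 than the marginal one when the strata are prognostic. Report a standardised risk difference beside it, on the same scale as the 26 points used for the sample size. Keep the treatment-only model as a sensitivity analysis.
- **Secondary outcomes.** Where birth weight is expected to be predictive, stratified tests may replace the crude ones (van Elteren, Cochran-Mantel-Haenszel, stratified log-rank).
- **Strata.** Restate the limits so that every birth weight falls in exactly one stratum, matching the boundary that the randomisation list actually uses.

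The cost is a few sentences of wording, with no new data and no change to the sample size, because birth weight is already recorded. The primary model should be fixed before the allocation code is broken. Any separate analysis plan should carry the same text.

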**Study outcome measures**

##### Study outcome measures

Primary outcome of the study is the effect of acidic and neutral oligosaccharides (20%/80% mixture) supplemented enteral feeding in a maximum doze of 1.5g/kg/day on infectious morbidity as previously defined.1,14 Furthermore, parameters of feeding tolerance, and short-term outcome are evaluated (Table 1). In addition to clinical outcome, intestinal permeability, faecal flora (including pH, viscosity measurements and acetate measurements), faecal IL-8 and calprotectin (Diagnostic Products Corporation Nederland BV), gastrointestinal transport time (by carmine red) and plasma cytokine concentrations (Il-2, Il-4, IL-5, IL-8, IL-10, TGFα , IFNγ,) are determined during the 30 day study period (Table 2).

*Clinical outcome measures*

The following perinatal characteristics are registered to assess prognostic similarity: maternal age and race, obstetric diagnosis, administration of antenatal steroids and antibiotics, mode of delivery, sex, gestational age, birth weight, birth weight <p10, Apgar scores, pH of the umbilical artery, clinical risk index for babies16 and administration of surfactant.

During the study period actual intake of enteral and parenteral nutrition, powder supplementation and type of feeding (breast milk or preterm formula) are recorded daily.

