Appendix 1: Case record form

Appendix 2: Questionnaire side effects vaccinations

**Tables**

### Table 1 Clinical outcome measures

|  |  | Remarks |
| --- | --- | --- |
| Infectious morbidity |  |  |
| Serious infections |  | Primary outcome |
| Number of infectious episodes |  |  |
| Cultured micro-organisms |  |  |
| Feeding tolerance |  |  |
| Enteral feeding >120 mL/kg/day |  |  |
| Age at finishing parenteral nutrition |  |  |
| Necrotising enterocolitis |  | Bell et al.[15] |
| Weight *z* scores at birth, day 30 and at discharge |  | Usher et al. [25] |
| Patent ductus arteriosus |  |  |
| Ventilatory support |  |  |
| Use of oxygen at postmenstrual age of 36 weeks |  | Jobe et al. [26] |
| Intraventricular hemorrhage |  | Papile et al. [27] |
| Retinopathy of prematurity |  | Committee for ROP [28] |
| Death |  |  |
| Age at discharge from NICU and at discharge home |  |  |
| ROP= retinopathy of prematurity; NICU = neonatal intensive care unit. | | |

Table 2: Study schedule

| **Postnatal age** |  | **< 48h** | **day 4** | **day 7** | **day 14** | **day 30** | **5 mo** | **1 yr** |
| --- | --- | --- | --- | --- | --- | --- | --- | --- |
| **Faeces** |  |  |  |  |  |  |  |  |
| Faecal  Calprotectin  /IL-8 |  | x | - | x | x | x | x | x |
| Intestinal  microflora  FISH / pH |  | x | - | x | x | x | x | x |
| Gastrointesti-  nal transport  time |  | - | - | - | x | - | - | - |
| **Urine** |  |  |  |  |  |  |  |  |
| Intestinal  permeability |  | x | x | x | - | - | - | - |
| **Blood** |  |  |  |  |  |  |  |  |
| Cytokine profile | 0,5ml | x | - | x | x | - | - | - |
| IgE/IgG4 | 0,6ml | - | - | - | - | - | x | x |
| Immune  response | 2,0ml | - | - | - | - | - | x | x |

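### The additional adjusted infection model takes breast milk without fixing it at baseline, picks further covariates by observed imbalance, and leaves out the birth-weight stratum

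*Protocol*

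**What the plan says.** The Statistical analysis section of the protocol has three relevant steps.

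- Balance check: "To determine whether randomisation is successful, prognostic similarity (perinatal and nutritional characteristics) between treatment groups is assessed".
- Crude analysis of the primary outcome: "Logistic regression is performed to examine whether acidic and neutral oligosaccharide supplemented enteral nutrition decreases the incidence of serious infections". No covariates are attached to it.
- Adjusted analysis: "In an additional analysis, adjustments are made for possible confounding factors". The named factors are antenatal corticosteroids and birth weight below the tenth centile, followed by "administration of breast milk and other prognostic factors that may be different between treatment groups".

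The timing is given elsewhere. Under Treatment allocation and blinding, infants are "randomly allocated to treatment <48 hours after birth", within three birth-weight strata. Under Study outcome measures, intake of enteral and parenteral nutrition, powder and "type of feeding (breast milk or preterm formula) are recorded daily" during the study period.

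The Background expects less feeding intolerance with the supplement. Table 1 lists feeding tolerance as an outcome, including reaching full enteral feeding and "Age at finishing parenteral nutrition".

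**The concern.** There are three defects in how the adjusted model is specified.

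1. **A covariate not tied to baseline.** Breast-milk administration may mean the first feed, the intended feed or the share of feeds over days 3 to 30. Only the first two can be settled before the supplement acts.
2. **An open list filled by observed differences.** A factor enters because it differs between arms, not because it predicts infection. No threshold is given, and strong predictors that happen to balance stay out. Since nutritional characteristics belong to the balance check, intake and feeding progress could be read as candidates. A difference there may be an effect of the supplement; it does not show that randomisation failed. It may also be a consequence of infection, because feeding problems count among the clinical signs of sepsis.
3. **The stratification factor is absent.** Birth-weight stratum is used to allocate but is not named in either infection model. The neurodevelopmental model in the same section does name gestational age and birth weight.

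At stake is the reading of the adjusted result next to the crude one. If they disagree, the protocol does not say in so many words which decides.

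**Working it through.** **The plan's own figure.** From the Sample size section: 2 × 7.85 × 0.63 × 0.37 / 0.26² = 54.1, so 54 per arm, which reproduces. It rests on an unadjusted comparison of 76% with 50%; power at 54 per arm is 80.8%. The crude odds ratio is (0.50/0.50)/(0.76/0.24) = 0.316.

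**Selection by imbalance.** The list registered to assess prognostic similarity has 14 items: maternal age, race, obstetric diagnosis, antenatal steroids, antenatal antibiotics, mode of delivery, sex, gestational age, birth weight, birth weight below the tenth centile, Apgar scores, cord pH, CRIB score and surfactant. With independent tests at 5%, the chance that at least one is flagged under perfect randomisation is 1 − 0.95^14 = 51%. Several items are correlated and birth weight is stratified, so 51% is an approximate upper figure. It measures how often the model would change by chance, not bias.

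Type I error was simulated at 54 per arm with no effect, 4,000 trials per setting, 10 to 15 independent prognostic candidates (assumed), and entry at p < 0.05 (assumed):

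| Quantity | Range over settings |
|---|---|
| Crude test | 4.6% to 5.3% |
| Adjusted test | 4.5% to 5.2% |
| Either test significant | 5.4% to 6.2% |
| Crude and adjusted disagree | 1% to 2% |

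**Breast milk as covariate.** Assumptions: 60% use in controls, odds ratio of breast milk for infection 0.3 to 0.5, total effect held at 76% versus 50%.

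| Difference in use, supplement minus control | Adjusted OR | Change in log OR against crude |
|---|---|---|
| 0 points | 0.29 to 0.31 | none lost (3% to 8% larger) |
| 5 points | 0.31 to 0.32 | 2% larger to 1% lost |
| 10 points | 0.33 | about 4% lost |
| 20 points | 0.35 to 0.38 | 10% to 14% lost |

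The gain in the first row arises because an odds ratio conditional on a prognostic factor lies further from 1 than the crude one. It does not signal bias.

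**A feeding-progress variable, if one entered.** Assumptions: 40% to 60% of controls have good progress, infection risk is 30 points lower with good progress, total effect 76% versus 50%, 54 per arm. Example with 50% of controls and a 20-point shift: control risks are 0.76 + 0.30 × 0.50 = 0.91 and 0.61; treated risks are 0.50 + 0.30 × 0.70 = 0.71 and 0.41. A logistic model with arm and progress was fitted to these expected proportions, with approximate Wald power.

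| Shift in good progress | Adjusted OR | Log OR lost | Power, adjusted |
|---|---|---|---|
| 0 points | 0.27 to 0.28 | none | 82% |
| 10 points | 0.32 to 0.33 | about 2% | 72% to 73% |
| 20 points | 0.38 | 15% to 17% | 59% to 60% |
| 30 points | 0.44 to 0.46 | 28% to 32% | 42% to 46% |

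The crude comparator by the same approximation: standard error √(1/(54 × 0.76 × 0.24) + 1/(54 × 0.25)) = 0.419, log OR −1.153, power Φ(1.153/0.419 − 1.96) = 79%.

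**The case against.** The best defence is that little depends on this model. It is labelled additional, it follows a crude regression, and the sample size rests on the crude comparison. That stands. A reader might infer that the primary result itself is compromised; the protocol does not support this.

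A reader might also infer that adjusting for breast milk will shrink the effect. The documents describe no route from supplement to breast-milk use. Feed type follows the parents' choice, parents and staff are blinded, powder goes into either feed, and minimal feeding starts on day 1, before supplementation on day 3. Being recorded after randomisation does not by itself make a variable a mediator. This stands, and the arithmetic agrees.

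A third tempting inference is that choosing covariates by imbalance invalidates the p value and confidence interval. The simulated type I error does not bear that out for the p value. The batch code is also broken only after analysis, so the analyst does not know which arm is active.

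The entry of feeding-progress variables is a possible reading and not a stated rule. The section on outcome measures ties only perinatal items to prognostic similarity. Against that, the Statistical analysis section expressly says that "prognostic similarity (perinatal and nutritional characteristics) between treatment groups is assessed", and the open clause excludes nothing. A statistical analysis plan, not shown, may close the list. The protocol's own wording still sets a rule that depends on observed differences.

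**Conclusion.** The point holds in a limited form, with minor to moderate severity. The additional model is not fixed in advance, its breast-milk term is not tied to a pre-allocation value, and the randomisation stratum is not named in it. The crude regression is unaffected.

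The effect on type I error is negligible: the adjusted test stays at 4.5% to 5.2%, rising to at most 6.2% if either test could claim success. Bias from breast milk alone is nil without an arm difference in use and modest with an assumed large one. The larger losses, up to about a third of the log odds ratio, need two things that the documents do not establish: that a feeding-progress variable enters, and that it shifts by arm and relates to infection as assumed. They illustrate the size of the risk; they do not predict this trial's result.

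The practical harms are discretion over which covariates enter, possible over-adjustment through nutritional variables, and no adjustment for the factor used to stratify allocation.

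**What to change.** In the Statistical analysis section:

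- State which logistic regression decides the primary question: the unadjusted one or one adjusted for birth-weight stratum.
- Replace the imbalance-driven clause with a closed list of pre-allocation covariates already collected: birth-weight stratum, gestational age, birth weight below the tenth centile, antenatal corticosteroids.
- Use feeding type only as initial or intended type at baseline, or in an analysis labelled as sensitivity.
- Remove nutritional characteristics from the check of randomisation and report them by arm as post-randomisation data.

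The cost is wording. The sample size stays at 54 per arm and no further infants are needed. The only possible extra is one case record form item, if intended feeding type is wanted and not already captured before allocation.

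### Weight z scores at day 30 and at discharge are to be compared unadjusted, although the birth z score and the birth-weight stratum are available and would make the comparison more precise

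*Protocol*

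**What the plan says.** The Statistical analysis section of the protocol sets out four kinds of analysis.

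- **Primary outcome:** logistic regression, followed by a second, adjusted model: "In an additional analysis, adjustments are made for possible confounding factors as administration of antenatal corticosteroids, birth weight <p10" and other factors.
- **Secondary outcomes:** "Analyses of secondary outcomes (only crude) is performed by Mann-Whitney U test", with chi-square, Fisher and log rank tests for the other data types. The parenthesis makes this a stated choice of unadjusted tests, not a silence.
- **Longitudinal markers:** these have their own sentence. GEE "are used to analyse changes over time in intestinal permeability, faecal microflora, faecal IL-8 and calprotectin, and plasma Th1/Th2 cytokine concentrations".
- **Neurodevelopment:** the comparison of arms "is examined by logistic regression with adjustments for possible confounding factors as gestational age and birth weight".

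Table 1, Clinical outcome measures, has one row for weight z "scores at birth, day 30 and at discharge". Under Treatment allocation and blinding, infants are stratified into three birth-weight groups and randomised within 48 hours of birth. Under Treatment, supplementation runs from day 3 to day 30. The Sample size section gives 54 infants per arm.

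**The concern.** Birth weight is known before allocation, because it defines the randomisation stratum. The birth z score is therefore a baseline measurement of the same quantity that is compared at day 30 and at discharge. An infant who is small for gestation at birth will tend to be small later. Comparing the later values without the birth value leaves that predictable variation in the error term.

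The plan is also uneven. It adjusts neurodevelopment for birth weight and gives the primary outcome a further model with birth weight below the 10th percentile. It rules out adjustment for growth, the outcome most directly tied to size at birth. At stake is the size of growth effect that a trial sized only for infections can detect or exclude.

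**Working it through.** **1. The plan's own sample size.** The Sample size section uses 2 × 7.85 × p(1−p)/d² with p = 0.63 and d = 0.76 − 0.50 = 0.26:

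2 × 7.85 × 0.63 × 0.37 / 0.26² = 3.660 / 0.0676 = 54.1, so 54 per arm. The figure reproduces. It refers to the primary outcome; no figure is given for any secondary outcome.

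**2. Detectable difference for a crude comparison of a continuous outcome.** With 54 per arm, two-sided α = 0.05 and 80% power, in units of the outcome SD:

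(1.960 + 0.842) × √(2/54) = 2.802 × 0.1925 = 0.539 SD.

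For the Mann-Whitney test under normality, with relative efficiency 3/π = 0.955, this becomes 0.539/√0.955 = 0.552 SD.

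**3. Effect of adjusting for the birth value.** ANCOVA multiplies the variance of the treatment difference by 1 − r², where r is the within-arm correlation between the birth and later z scores. The detectable difference is then 0.539 × √(1 − r²), and the equivalent crude sample size is 54/(1 − r²). The protocol gives neither r nor an SD, so r is an assumption shown over a range.

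| Assumed r | Variance remaining | Variance removed | Detectable difference (SD) | Equivalent crude n per arm |
|---|---|---|---|---|
| 0.5 | 0.75 | 25% | 0.467 | 72 |
| 0.7 | 0.51 | 49% | 0.385 | 106 |
| 0.9 | 0.19 | 81% | 0.235 | 284 |

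For a true difference of 0.539 SD, power rises from 80% to 89.9% at r = 0.5 and to 97.5% at r = 0.7. At r = 0.2 the gain would be negligible (variance × 0.96, power 81.6%).

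**4. Allowance for stratification.** The formula in step 3 takes simple randomisation as the reference. Here allocation is stratified by birth weight in blocks of four, which already removes some of the chance difference in birth size. The gain over the crude difference may therefore be somewhat smaller than in the table. Strata based on grams do not fully balance a weight-for-gestation score, so the stratum does not replace the birth z score as a covariate.

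**5. Reach.** The 1 − r² calculation applies to continuous outcomes that have a baseline counterpart. In Table 1 that is the weight z score row. It does not carry over directly to binary or time-to-event outcomes.

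**The case against.** The strongest reply is that nothing here is invalid. Under randomisation the crude test keeps its type I error, and its standard error already allows for chance imbalance at birth. That stands: imbalance and unexplained variance are one loss, not two, and the loss is efficiency. It is also fair that only one row of Table 1 is affected, that growth is not named separately in the protocol's aims, and that every correlation used above is assumed.

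A second reply is that listing the birth z score in Table 1 merely names the time points of one measure. Birth weight is already registered as a perinatal characteristic for checking prognostic similarity. That also stands, as the protocol nowhere says that the birth value will be tested as a treatment effect. Calling it a baseline variable is a clarification; the substance is its use in the later comparison.

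A reader might go further and infer that the <48 h values of permeability, microflora, faecal IL-8 and calprotectin, and cytokines are discarded too. The documents do not support this. The sentence on unadjusted tests does not govern these markers. The next one sends them to GEE, whose methods "are used to analyse changes over time in intestinal permeability, faecal microflora, faecal IL-8 and calprotectin" among others, and an analysis of change over a series that begins with the <48 h sample in Table 2 can use that sample. The protocol neither states nor excludes a baseline term, and the model terms are detail that an analysis plan may supply. A precision loss calculated against a crude comparison at a single later visit would not describe the planned analysis of these markers.

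**Conclusion.** The point holds for weight z scores at day 30 and at discharge. The protocol explicitly chooses an unadjusted comparison where a pre-treatment value of the same measure and the randomisation stratum are both available. The crude result would be valid but less precise than the data allow.

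The size depends on the unknown correlation. A central assumption of 0.7 brings the detectable difference from about 0.54 SD to 0.385 SD, roughly what doubling the trial would achieve (106 against 54 per arm). The figures also assume complete weights in 54 infants per arm and an approximately linear relation between birth and later z scores, and stratified allocation may reduce the gain. This is a free improvement to one secondary measure. It does not show bias, does not touch the primary outcome, and does not reach the GEE analyses.

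**What to change.** In the Statistical analysis section, exempt the weight z scores from the restriction to unadjusted tests. Name the birth weight z score as a baseline variable. Analyse the day-30 and discharge z scores by ANCOVA with terms for treatment, birth z score and birth-weight stratum, and report the adjusted mean difference with its 95% confidence interval. Keep the planned crude test as a supportive analysis.

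The cost is a change of wording: the weights and strata are already recorded. Because the protocol has the data analysed as treatments A and B before the code is broken, the change should be fixed before any comparison of A with B is made.
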